# Efficacy of modified Banxia Xiexin decoction in the management of *Wei-Pi* syndrome (postprandial distress syndrome): study protocol for a randomized, waitlist-controlled trial

**DOI:** 10.1186/s13063-021-05078-y

**Published:** 2021-02-12

**Keywords:** Banxia Xiexin decoction, Chinese medicine, *Wei-Pi* syndrome, Postprandial distress syndrome, Functional dyspepsia, Quality of life, Randomized controlled trial, Study protocol

## Abstract

**Background:**

Postprandial distress syndrome manifests as a feeling of fullness and early satiation that can significantly reduce the quality of life of the patients. In Chinese medicine (CM), the syndrome is traditionally regarded as the *Wei-Pi* syndrome, and Banxia Xiexin decoction (BXD) has been used in the empirical treatment of the same for a long time. The current study aims to evaluate the efficacy of modified BXD in the management of *Wei-Pi* syndrome.

**Methods/design:**

A randomized, waitlist-controlled trial will be conducted. A total of 84 patients with *Wei-Pi* syndrome will be randomized into the BXD or waitlist control group in a ratio of 1:1. The patients in the BXD group will receive the semi-individualized BXD on the basis of the syndrome differentiation in CM, for a duration of 3 weeks and will be under follow-up for further 3 weeks after the completion of therapy. Conversely, the patients in the waitlist control group will undergo the same intervention and follow-up after a 3-week waiting period. In the current study, the primary outcome will be the variation in the scores pertaining to the global scale of the Quality of Life Questionnaire for Functional Digestive Disorders after 3 weeks. The secondary outcomes include the variations in the scores pertaining to the Hospital Anxiety and Depression Scale and the EuroQoL 5-dimension 5-level Questionnaire and the results of the liver and kidney function tests.

**Discussion:**

This trial will assess the efficacy of modified BXD in improving the clinical symptoms and quality of life of the patients suffering from *Wei-Pi* syndrome.

**Trial registration:**

ClinicalTrials.govNCT04398888. Registered on May 21, 2020

**Supplementary Information:**

The online version contains supplementary material available at 10.1186/s13063-021-05078-y.

## Background

Functional dyspepsia (FD) is a chronic disorder of the upper digestive tract that manifests as pain or discomfort in the upper abdomen, or a feeling of bloating, belching, fullness, and heartburn [1]. The estimated incidence of FD in the Western countries is 10 to 40% and 5 to 30% in Asia [2]. In Hong Kong, 14.6 to 18.4% of the population is affected by dyspepsia [3, 4]. The disorder imposes a significant social and economic burden on a global scale. For instance, the annual economic burden amounts to £1 billion in the UK and $18.4 billion in the USA [5, 6].

In accordance with the Rome IV criteria, FD has two subgroups: (1) epigastric pain syndrome—the patients predominantly suffer from epigastric pain or burning; (2) postprandial distress syndrome (PDS)—the patients experience a feeling of fullness and early satiation [1]. *Wei-Pi* is a term associated with gastrointestinal disorders, which is documented in the ancient Chinese medical classic, the *Huangdi’s Internal Classic* [7]. The patients with the disorder display diminution or loss of appetite, epigastric distention, and feeling of fullness. The ingestion of food aggravates the aforementioned symptoms, whereas belching relieves the same [8, 9]. As per the consensus of the China Association of Chinese Medicine (branch of Gastrointestinal Diseases), the *Wei-Pi* syndrome in Chinese medicine (CM) is equivalent to the PDS [8, 9].

A unique feature of CM is the treatment based on syndrome differentiation, wherein the patient receives an individualized herbal prescription, in line with the body constitution of the patient and the pathological factors associated with the symptoms [10, 11]. The common pathological factors that contribute to the *Wei-Pi* syndrome include exterior pathogen invasion, food stagnation, phlegm stagnation, mental dissatisfaction, and spleen-stomach vacuity [12]. *Wei-Pi* syndrome is differentiated into five patterns in Chinese medicine (CM): (1) spleen deficiency and qi stagnation, (2) liver qi invading the stomach, (3) spleen-stomach dampness-heat, (4) spleen-stomach deficiency cold, and (5) cold-heat complex pattern [8, 9]. Banxia Xiexin decoction (BXD), first documented in the CM classic, the *Treatise on Cold Damage and Miscellaneous Diseases*, is a classic formulation for the treatment of *Wei-Pi* syndrome with the cold-heat complex pattern [8, 9]. BXD is used to direct the qi downwards, in order to relieve the hiccup, dissipate the fullness and satiation, and harmonize the cold-heat in the patient’s stomach. As the clinical manifestation of symptoms may vary from patient to patient, general clinical practice adopts an approach that involves the addition of specific herbs to the BXD, in accordance with the respective syndrome differentiation (termed modified BXD). Recent clinical studies have reported that BXD is effective in the treatment of *Wei-Pi* syndrome and improves the symptoms of FD by regaining the gastric emptying rate, reducing the mucosal damage, improving the gastrointestinal function, and inducing anti-inflammatory action against *Helicobacter (H.) pylori* [13–15]. However, evidence regarding the effect of BXD on FD remains inconclusive, on account of the methodological flaws in the aforementioned studies.

The present study aims to evaluate the efficacy of modified BXD in the management of *Wei-Pi* syndrome through a randomized, waitlist-controlled trial. A semi-standardized treatment protocol based on syndrome differentiation will be adopted, in order to fulfill the CM theory on diagnosis and treatment, and to ensure scientific rigor of the trial design. A waitlist control group will be used, owing to the unavailability of an inert placebo for BXD.

## Methods/design

### Study design

This is a randomized, waitlist-controlled trial to evaluate the efficacy of semi-standardized BXD in patients with *Wei-Pei* syndrome. The study protocol follows the Declaration of Helsinki and the guidelines of the Standard Protocol Items: Recommendations for Interventional Trials (SPIRIT) and has been approved by the Institutional Review Board of the University of Hong Kong/Hospital Authority Hong Kong West Cluster (HKU/HA HKW IRB, UW 20-216) in May 2020.

### Patient recruitment

This trial will be conducted in the Hong Kong Buddhist Association-The University of Hong Kong Clinical Centre for Teaching and Research in Chinese Medicine (HKBA-HKU CMCTR). The subjects will be recruited using posters, webpage, Facebook page, and magazines pertaining to the Hong Kong Buddhist Association and through public dialogs and interviews in the local media. The lead investigator ([name]) will be responsible for the identification of potential recruits and obtaining informed consent. A flowchart of the study is shown in Fig. 1. The proposed project schedule is shown in Tables 1 and 2.

**Fig. 1 Fig1:**
[figure not shown]
Flow diagram of patient recruitment

**Table 1 Tab1:** Assessment timetable for the treatment group

	Telephone screening	Screening	Baseline (Wk 0)	Intervention			Follow-up	
				Wk 1–Wk 3			Wk 4	Wk 6
Visit number	0	1	2	3 (tel)	4 (tel)	5	6 (tel)	7
Day	− 28 to − 14	− 13 to − 7	0	7 ± 2	14 ± 2	21 ± 2	28 ± 2	42 ± 3
Screening information	✓	✓						
Informed consent		✓						
Review In/Ex criteria	✓	✓	✓	✓	✓	✓	✓	✓
Medical history	✓		✓					
Demographics			✓					
Blood test		✓					✓	
Primary outcome								
*FDDQL*			✓			✓		✓
Secondary outcomes								
*HADS*			✓			✓		✓
*EQ-5D-5L*			✓	✓	✓	✓	✓	✓
*Concomitant medications*	✓	✓	✓	✓	✓	✓	✓	✓
*Safety and tolerability*				✓	✓	✓		

*EQ-5D-5L* EuroQoL 5-dimension 5-level, *FDDQL* Quality of Life Questionnaire for Functional Digestive Disorders, *HADS* Hospital Anxiety and Depression Scale (HADS), *In/Ex* inclusion and exclusion, *Tel* telephone interview, *Wk* week

**Table 2 Tab2:** Assessment timetable for the waitlist group

	Telephone screening	Screening	Baseline (Wk0)	Waiting period			Intervention			Follow-up	
				Wk1	Wk2	Wk3	Wk4–Wk6			Wk 7	Wk 9
Visit number	0	1	2	3 (tel)	4 (tel)	5	6 (tel)	7 (tel)	8	9 (tel)	10
Day	− 28 to − 15	− 13 to − 7	0	7 ± 2	14 ± 2	21 ± 2	28 ± 2	35 ± 2	42 ± 2	49 ± 2	63 ± 3
Screening information	✓	✓									
Informed consent		✓									
Review In/Ex criteria	✓	✓	✓	✓	✓	✓	✓	✓	✓	✓	✓
Medical history	✓		✓								
Demographics			✓								
Blood test		✓								✓	
Primary outcome											
*FDDQL*			✓			✓			✓		✓
Secondary outcomes											
*HADS*			✓			✓			✓		✓
*EQ-5D-5L*			✓	✓	✓	✓	✓	✓	✓	✓	✓
*Concomitant medications*	✓	✓	✓	✓	✓	✓	✓	✓	✓	✓	✓
*Safety and tolerability*							✓	✓	✓		

*EQ-5D-5L* EuroQoL 5-dimension 5-level, *FDDQL* Quality of Life Questionnaire for Functional Digestive Disorders, *HADS* Hospital Anxiety and Depression Scale (HADS), *In/Ex* inclusion and exclusion, *Tel* telephone interview, *Wk* week

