### Randomization

In the present study, 84 patients with *Wei-Pi* syndrome will be randomized into the BXD or waitlist control group in a 1:1 ratio, after obtaining informed consent. The block randomization method will be employed; random codes will be generated by means of the SPSS software and placed in opaque envelopes. The principal investigator will be responsible for the maintenance of the opaque envelopes.

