#### Control group

The patients in the waitlist control group will be under observation during the 3-week waiting period. Subsequently, they will undergo the same treatment and follow-up as the BXD group, in order to minimize the nocebo effect.

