#### Concomitant treatment

Medications and standard care for postprandial distress syndrome will not be restricted. A patient diary will be used to document the use of medications and adverse events in the patients.

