### Follow-up

All the patients will be under follow-up for a time period of 3 weeks after the completion of treatment by means of telephonic interviews or face-to-face evaluations. The schedule pertaining to the BXD and waitlist groups is shown in Tables 1 and 2, respectively. The reasons for patient dropouts or withdrawals will be recorded in the case report form.

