##### Adverse events

Subjects will be asked to report any adverse events according to the monitoring form in the patient diary. The self-rated intensity of adverse events (mild, moderate, severe) and perceived causal relationship to intervention (unrelated, unlikely, possibly related, probably related, definitely related) will be recorded [25].

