#### Liver and kidney function tests

All the patients will undergo liver and kidney function tests twice (prior to and after the administration of modified BXD).

In the event of the incidental detection of abnormal liver and/or kidney functions after the consumption of Chinese medicine, the patient will be referred to a doctor for further examination, monitoring, and/or treatment.

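### Tables 1 and 2 schedule safety assessment only at visits on BXD, while the text sets no such limit; followed as scheduled, adverse events are ascertained unequally in the two randomised groups over days 0–21

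*Protocol article*

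**What the plan says.** The schedule is in the two timetables under Patient recruitment. In Table 1 (BXD group) the row "Safety and tolerability" is ticked at visits 3, 4 and 5 (days 7, 14 and 21) and left blank at follow-up visits 6 and 7. In Table 2, headed "Assessment timetable for the waitlist group", the same row is ticked at visits 6, 7 and 8 (days 28, 35 and 42). It is blank at visits 3–5, the waiting period, and at follow-up visits 9 and 10.

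The text is wider. Under Concomitant treatment: "A patient diary will be used to document the use of medications and adverse events in the patients". Under Adverse events, which is listed among the secondary outcomes: "Subjects will be asked to report any adverse events according to the monitoring form in the patient diary". Neither sentence is confined to a group or a period. The opening of Secondary outcomes refers the reader to Tables 1 and 2 for the timing of those outcomes.

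On the waiting group: "The patients in the waitlist control group will be under observation during the 3-week waiting period". On follow-up: "All the patients will be under follow-up for a time period of 3 weeks after the completion of treatment". On laboratory safety: "All the patients will undergo liver and kidney function tests twice (prior to and after the administration of modified BXD". Both tables place the second blood test at the first follow-up contact.

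**The concern.** Adverse events are a stated secondary outcome, and days 0–21 are the only time when patients randomised to BXD can be compared with patients randomised to wait. These patients have a chronic complaint with gastrointestinal symptoms, and their other medication is unrestricted, so some events will occur without BXD. A concurrent waitlist rate is what separates that background from an effect of the decoction.

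The rate serves this purpose only if events are looked for in the same way in both groups. A schedule that asks one group at three contacts and the other at none makes the two rates non-comparable. Interpretation then leans on each patient's own rating of causality, in an open-label trial where patients know their allocation. In follow-up, symptoms that begin after the last dose have no scheduled enquiry in either group.

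**Working it through.** The plan gives no figure to reproduce on this point. The check is a count of ticks by visit, set beside the text.

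**Scheduled safety and tolerability assessments per patient (Tables 1 and 2)**

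| Period | BXD group | Waitlist group |
|---|---|---|
| Days 0–21 (visits 3–5 in both) | 3 of 3 contacts, on BXD | 0 of 3 contacts, waiting |
| Waitlist group's own BXD course (visits 6–8) | not applicable | 3 of 3 contacts |
| Follow-up (BXD visits 6–7; waitlist visits 9–10) | 0 of 2 contacts | 0 of 2 contacts |

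Allocation is "84 patients with *Wei-Pi* syndrome will be randomized into the BXD or waitlist control group in a 1:1 ratio", which is 84 / 2 = 42 per group. With complete attendance, the randomised window holds 42 × 3 = 126 scheduled assessments on BXD and 42 × 0 = 0 on the waitlist.

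**The contacts exist.** Visits 3–5 fall on days 7, 14 and 21 in both groups. EQ-5D-5L and concomitant medications are ticked at all 5 post-baseline contacts in Table 1 and all 8 in Table 2, including those where the safety row is blank.

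**Laboratory tests do not fill the gap.** After screening, the next blood test is at day 28 in the BXD group and day 49 in the waitlist group. Each falls 7 days after that group's last treatment visit (28 − 21 and 49 − 42). Between screening and day 21 there are 0 tests in either group, and the waitlist test follows that group's own BXD course. The tests cover AST, ALT and creatinine, and do not record symptoms.

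**Table against text.** One diary carries both medications and adverse events. The tables tick medications at every contact but safety only on BXD. If the diary was meant to run throughout, the tables omit the matching safety review. If the tables are as intended, the two sentences on the diary are too broad.

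**Direction of the bias.** Let p_B and p_W be the true incidences over days 0–21. Let s_B be the chance that an event is recorded with scheduled enquiry plus diary, and s_W the chance with diary only. The expected observed difference is

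s_B·p_B − s_W·p_W = s_B·(p_B − p_W) + p_W·(s_B − s_W).

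The second term is the artefact. It is zero only if s_B = s_W (or p_W = 0). If scheduled enquiry raises recording, then s_B > s_W and the term is positive, so BXD shows an excess even when p_B = p_W. The documents give none of these four quantities, so the direction can be stated but not the size.

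**The case against.** The strongest reply is that the diary already covers what the tables leave out. Neither sentence about it restricts group or period, so waitlist patients may well be recording events from day 0. The table row is also undefined: it could mean a staff review of how the decoction is tolerated, for which ticks only during treatment would be natural. The article condenses a fuller protocol, which may say when diaries are issued and collected, and how adverse events are compared is usually settled in the analysis plan.

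Much of this stands. A reader might infer from the tables that adverse events are never recorded off BXD, that the randomised safety comparison is lost, or that nothing is sought after treatment. The documents do not support those readings. The diary has no stated limit. A liver and kidney test falls in follow-up in both groups. Under Oversight and monitoring, adverse events go to the trial monitoring committee quarterly and serious ones immediately to it and the review board, with no period named. It would be wrong to say that no control data will exist.

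It is also true that the comparison will be imprecise. With 42 per group the standard error of a difference in incidence is at most √(2 × 0.5 × 0.5 / 42) = 0.109, so a 95% interval could extend up to 1.96 × 0.109 = 0.21, or 21 percentage points, either side.

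The reply does not remove the point. Adverse events sit under a heading that sends the reader to Tables 1 and 2 for timing, and no other row in those tables fits them except the blood test. Even with diaries in both groups, one group is also asked at three contacts and the other is not. Wide intervals are no reason to accept a bias that can be removed. This is a printed schedule in conflict with the printed text, not a detail left out for brevity.

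**Conclusion.** The point holds as an inconsistency with a practical consequence. The tables tie scheduled safety assessment to BXD treatment visits, and the text on diary reporting does not. Followed as scheduled, ascertainment over days 0–21 is 3 assessments per BXD patient against 0 per waitlist patient, which biases the only randomised safety comparison, most likely towards more events on BXD. In follow-up there is one laboratory test per patient and no scheduled enquiry about symptoms or tolerability at the 2 contacts.

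This rests on two assumptions: that sites follow the timetable as printed, and that scheduled enquiry captures more events than an unprompted diary. The size of the bias cannot be derived from the documents. The FDDQL primary outcome is not touched. The change is worth making because it is nearly free and because data not collected at these contacts cannot be recovered by later analysis.

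**What to change.** Reconcile Tables 1 and 2 with the Concomitant treatment and Adverse events sections. Add the safety and tolerability tick at waitlist visits 3–5 and 9–10 and at BXD visits 6–7, and use the same diary form and the same questions in both groups. State that the diary runs from day 0 to the last follow-up visit. Waiting patients have no intervention to rate causality against, so the form should allow for that.

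Compare the incidence of all adverse events, whatever their rated causality, by randomised group over days 0–21.

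The cost is 5 extra assessments per waitlist patient and 2 per BXD patient, at most 42 × 5 + 42 × 2 = 294 in the whole trial. Each takes a few minutes at a contact where EQ-5D-5L and medications are already collected, so no visits are added.

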### Inclusion criteria

The patients have to meet the following criteria:
Permanent residents of Hong Kong with ages ranging from 18 to 60 years.Diagnosed with *Wei-Pi* syndrome with one or both of the following symptoms: (i) bothersome postprandial fullness, which occurs after the consumption of regular-sized meals with a minimum frequency of 3 days per week; (ii) bothersome early satiation that prevents the completion of a regular-sized meal, which occurs at a frequency of at least 3 days per week for the past 3 months; the time of onset of symptoms should be at least 6 months prior to the diagnosis [1, 9].

### Exclusion criteria

The patients will be excluded on the basis of the following criteria:
Pregnancy or patients planning conceptionAbnormal liver function; patients with more than two times the upper limit of the normal range of aspartate transaminase (AST) and alanine aminotransferase levels (ALT) [16]Abnormal kidney function with an estimated creatinine clearance below 80 mL/min [17]History of diagnosis of gastric structural abnormalities by means of endoscopy or history of gastrectomyGlucose-6-phosphate dehydrogenase deficiencyAlcohol or drug abuseConsumption of Chinese medicine within 1 month prior to the commencement of the studyUnable to read/understand and sign the informed consent document

### Randomization

In the present study, 84 patients with *Wei-Pi* syndrome will be randomized into the BXD or waitlist control group in a 1:1 ratio, after obtaining informed consent. The block randomization method will be employed; random codes will be generated by means of the SPSS software and placed in opaque envelopes. The principal investigator will be responsible for the maintenance of the opaque envelopes.

### Blinding

This is an open-label study. The patients and Chinese medicine practitioners (CMPs) will be informed regarding the allocation of patients into the two groups. CMPs will perform syndrome differentiation and prescribe the modified BXD, in accordance with the patient’s pattern of differentiation. The investigators who assess the outcomes will be blinded to the allocation and will not be involved in the diagnosis and treatment. Moreover, the coded information pertaining to the patients will be used for data entry and data analysis, and the group allocations will be masked during this process.

### Intervention

#### Treatment group

Patients will be treated by CMPs with a minimum of 5 years of clinical experience. The CMPs will differentiate the syndrome and prescribe herbal medicines for the individual patient, in accordance with the semi-standardized protocol, which consists of BXD and additional herbs (Table 3).

**Table 3 Tab3:** A modified BXD based on CM syndrome differentiation

Base decoction	Additional herbs when the following symptoms present
Pinellia ternate (Ban Xia) 9 g, Scutellariae Radix (Huang Qin) 9 g, *Coptis chinensis* (Huang Lian) 3 g, Zingiberis Siccatum Rhizoma (Gan Jiang) 6 g, Codonopsis Radix (Dang Shen) 9 g, Radix Glycyrrhizae (Gan Chao) 6 g, *Ziziphus zizyphus* (Da Zao) 6 g, *Cyperus rotundus* (Xiang Fu) 9 g, Hordei Fructus Germinatus (Sheng Mai Ya) 15 g	***Loss of appetite and fatigue*****:** Atractylodes Macrocephala (Bai Zhu) 12 g, Codonopsis Radix (Dang Shen) 15 g (total dosage) ***Abdomen symptoms relieved by pressure and warming***: Tetradium Ruticarpum (Wu Zhuyu 5 g) ***Bitter taste, xerostomia, nausea, and yellow coating of tongue***: Gardeniae Fructus (Zhi Zi) 9 g, ArtemisiacapillarisThunb (Yin Chen) 12 g ***Gastric acid reflux***: Sepiae Endoconcha (Hai Piaoxiao) 10 g, Concha Arcae (Wa Lengzi) 15 g

The modified decoction will be prepared by means of a conventional decocting method at the HKBA-HKU CMCTR, and the auto-decocting machines will pack the decoction in bags. The patients will be instructed to consume the decoction twice per day, 5 days per week, for 3 weeks.

#### Control group

The patients in the waitlist control group will be under observation during the 3-week waiting period. Subsequently, they will undergo the same treatment and follow-up as the BXD group, in order to minimize the nocebo effect.

#### Concomitant treatment

Medications and standard care for postprandial distress syndrome will not be restricted. A patient diary will be used to document the use of medications and adverse events in the patients.

